## Abstract

**Background:**

Patients diagnosed with idiopathic mild to moderate carpal tunnel syndrome (CTS) are usually managed in primary care and commonly treated with night splints and/or corticosteroid injection. The comparative effectiveness of these interventions has not been reliably established nor investigated in the medium and long term. The primary objective of this trial is to investigate whether corticosteroid injection is effective in reducing symptoms and improving hand function in mild to moderate CTS over 6 weeks when compared with night splints. Secondary objectives are to determine specified comparative clinical outcomes and cost effectiveness of corticosteroid injection over 6 and 24 months.

**Method/Design:**

A multicentre, randomised, parallel group, clinical pragmatic trial will recruit 240 adults aged ≥18 years with mild to moderate CTS from GP Practices and Primary-Secondary Care Musculoskeletal Interface Clinics. Diagnosis will be by standardised clinical assessment. Participants will be randomised on an equal basis to receive either one injection of 20 mg Depo-Medrone or a night splint to be worn for 6 weeks. The primary outcome is the overall score of the Boston Carpal Tunnel Questionnaire (BCTQ) at 6 weeks. Secondary outcomes are the BCTQ symptom severity and function status subscales, symptom intensity, interrupted sleep, adherence to splinting, perceived benefit and satisfaction with treatment, work absence and reduction in work performance, EQ-5D-5L, referral to surgery and health utilisation costs. Participants will be assessed at baseline and followed up at 6 weeks, 6, 12 and 24 months. The primary analysis will use an intention to treat (ITT) approach and multiple imputation for missing data. The sample size was calculated to detect a 15 % greater improvement in the BTCQ overall score in the injection group compared to night-splinting at approximately 90 % power, 5 % two-tailed significance and allows for 15 % loss to follow-up.

**Discussion:**

The trial makes an important contribution to the evidence base available to support effective conservative management of CTS in primary care. No previous trials have directly compared these treatments for CTS in primary care populations, reported on clinical effectiveness at more than 6 months nor compared cost effectiveness of the interventions.

**Trial registration:**

Trial registration: EudraCT 2013-001435-48 (registered 05/06/2013), ClinicalTrials.gov NCT02038452 (registered 16/1/2014), and Current Controlled Trials ISRCTN09392969 (retrospectively registered 01/05/2014).

**Electronic supplementary material:**

The online version of this article (doi:10.1186/s12891-016-1264-8) contains supplementary material, which is available to authorized users.

## Background

Carpal tunnel syndrome (CTS) is caused by compression of the median nerve as it passes through the carpal tunnel [1]. CTS leads to difficulties with day-to-day tasks and reduces capacity to work impacting on quality of life and general health [2–4]. Incidence rates in the general population have been estimated at 61–120 per 100,000 women and 35–60 per 100,000 men per year [5].

CTS is characterised by pain, paraesthesia and numbness in the median nerve distribution; usually worse at night causing sleep disruption, and may be alleviated by shaking the hand. Over half of patients have bilateral symptoms and the age distribution is bimodal peaking in the 50–54 and 75–84 age groups [1, 5–8].

There is no consensus on the best treatment for CTS, especially in primary care [9]. Surgical decompression is often considered the definitive solution to resolve symptoms in severe or unresponsive cases. Systematic review evidence comparing surgical with non-surgical treatments concluded that surgery produced superior results to splinting, but evidence for the benefit of surgery over corticosteroid injection was unclear [10]. In patients who have surgery up to 8 % are left with worse or unimproved symptoms [11].

The most commonly used treatments for mild/moderate CTS in primary care are splinting, anti-inflammatory medication and local corticosteroid injection [9, 12]. Systematic reviews of these treatments [9, 13–15] draw similar conclusions of moderate evidence in the short term for nocturnal hand bracing/splinting being more effective than no therapy (relative risk for overall improvement in symptom and function = 4.00; 95 % CI, 2.34–6.84) with limited evidence of medium term effects [9] and moderate to strong evidence for the effectiveness of corticosteroid injections over placebo (relative risk in terms of success rate: 2.58; 95 % CI, 1.72–3.87) in the short term [9]. In one primary study [16] of corticosteroid injections, higher doses (60 mg) appeared more effective than lower doses (20 or 40 mg) in the medium term (success rates for high dose 73 % versus 53-56 %) although the benefits were not maintained in the long term. Two injections of 15 mg steroid did not provide any additional clinical benefit over a single treatment [9]. Review authors conclude that many of the included trials had a high risk of bias and recommended that more robust trials are needed to compare treatments and ascertain the medium to long-term benefits [9, 13–15].

The effects of corticosteroid injection and splinting have been compared in two small trials, neither of which were carried out in a primary care setting. Sevim and colleagues showed superior effects of splinting over corticosteroid injection (*n* = 30) [17] and Ucan et al. found no significant differences in clinical outcome when comparing splinting (23 hands) to a combination of injection with splinting (23 hands) although both groups improved [18]. Robust inferences cannot be made from these studies.

We have therefore designed and are currently implementing a prospective randomised clinical trial to directly compare the clinical and cost-effectiveness of night splinting and corticosteroid injections as primary care management interventions for CTS.

## Methods

### Aim

The primary objective of the INSTINCTS trial is to investigate whether a corticosteroid injection is clinically effective in reducing symptoms and improving function in the short term (6 weeks) compared to a resting night splint in people consulting with mild to moderate carpal tunnel syndrome in primary care.

The secondary objectives are to examine clinical and cost effectiveness in the medium term (6 months) of a single corticosteroid injection compared to night splinting, from a healthcare (NHS) and personal social services perspective as well as from a societal perspective to include the differences in productivity loss. In the longer term (24 months) we will examine differences in symptoms, function, work absence, and other health care resource use, in particular, referral for CTS surgery.

### Design

The trial is a randomised, multicentre, open label, parallel group, pragmatic clinical trial comparing a single injection of Methylprednisolone Acetate (as 20 mg of Depo-Medrone 40 mg/ml) into the carpal tunnel versus 6 weeks of night splinting in patients with mild to moderate CTS.

### Eligibility criteria

The eligibility criteria (Table 1) are designed to select a relatively homogeneous group of patients with CTS, suitable for both splinting and local injection and who do not require immediate onward referral for surgery. For participants with bilateral CTS a study hand will be designated by the participant based on the most severe symptoms. Patients will not be allowed to enter the trial more than once.

**Table 1 Tab1:** Eligibility criteria

Inclusion criteria	Exclusion criteria
Male or female aged ≥ 18 years	Corticosteroid injection or night splints for CTS in the affected wrist within preceding 6 months
A clinical diagnosis of unilateral or bilateral CTS as made by a GP or trained clinician according to the diagnostic criteria	Severe CTS exhibiting constant numbness or pain, constant sensory loss, severe Thenar muscle atrophy or symptom severity which requires the patient to be referred for a surgical opinion
Mild (e.g. intermittent paraesthesia) or moderate (e.g. constant paraesthesia, reversible numbness and/or pain) severity CTS of idiopathic nature	Any previous surgery on the affected wrist (or study wrist in the case of bilateral symptoms)
Symptom duration of episode of at least 6 weeks	Clinical suspicion of local or systemic sepsis or infection
Written informed consent provided by the patient, prior to any trial specific procedures	Current or previous infection of the affected wrist
	Trauma to the affected hand requiring surgery or immobilisation in the previous 12 months
	Unable to tolerate the study interventions
	Unable to understand and complete self-report questionnaires written in English
	Inter-current illness including, but not limited to: • poorly controlled thyroid disease • poorly controlled diabetes mellitus • vibration-induced neuropathy • inflammatory joint disease • suspected complex neurological conditions • any other severe medical illness which in the opinion of the local Principal Investigator (or other authorised clinical delegate) precludes trial participation
	Pregnant or lactating females
	Receiving anticoagulants
	Any history of hypersensitivity to Depo-Medrone or any of its excipients
	Allergy to any of the splint materials
	Known abuse of drugs or alcohol
	Involved in on-going litigation cases for their condition

### Inclusion criteria

The study population will consist of adults aged 18 years and over with a new episode of primary idiopathic mild to moderate CTS which has been present for more than 6 weeks. Clinical diagnosis will be made by a GP or trained clinician and standardised based on presenting symptoms, clinical history and physical tests using criteria developed as part of a consensus survey of GPs from the UK Primary Care Rheumatology Society [12]. Mild CTS is defined as intermittent paraesthesia in the distribution of the median nerve and moderate as constant paraesthesia, reversible numbness and/or pain of idiopathic nature [19].

### Exclusion criteria

Participants will be ineligible for the trial if they have received either a corticosteroid injection or night splints for CTS within preceding 6 months or had previous surgery in the affected wrist (or study wrist in the case of bilateral symptoms), severe CTS exhibiting constant numbness or pain, constant sensory loss, severe thenar muscle atrophy or symptom severity which requires the patient to be referred for a surgical opinion. Other exclusion criteria are listed in Table 1.

### Recruitment, screening process and enrolment

Participants will be recruited from up to 50 sites including; GP practices, primary-secondary care musculoskeletal interface clinics throughout the UK. Research sites will have received NHS permission and trial specific training covering the interventions and trial administrative procedures (Additional file 1).

### General practice recruitment

For patients consulting in general practice, who are diagnosed with mild-moderate CTS and are eligible to participate, information about the trial will initially be provided verbally by their GP. Interested eligible patients will be given a participant information leaflet. Patients will be asked to give written consent to provide their personal details to Keele University. This will permit contact by a Clinical Research Network Nurse who will provide a full verbal explanation of the trial for the patient to consider. This will include detailed information about the rationale, design and personal implications of the trial. The patients will be advised by the GP that consent to contact does not oblige them to take part in the trial. For patients willing to participate, a second appointment for randomisation and treatment with the treating clinician will be made (within a minimum of 24 h and a maximum of 4 weeks’ time). On attendance at their scheduled second appointment, the patient’s GP will check for continued eligibility for inclusion and gain written informed consent to study participation from those eligible patients willing to take part in the study.

### Primary/Secondary care musculoskeletal interface clinics recruitment

For patients consulting at musculoskeletal interface or similar clinics based in secondary care, patients will be informed verbally about the trial by a study clinician following an initial clinical assessment. Eligible patients who are interested will be provided with an information leaflet. When the patient has had adequate time to read the information, a study clinician will give full details of the trial and answer any questions. Those patients willing to take part will be required to provide full written consent. A list of sites at which patients will be recruited is provided as Additional file 1.

### Randomisation

Prior to randomisation all participants will complete the baseline questionnaire, which includes questions regarding sociodemographic characteristics, outcome measures and potential prognostic factors. Participants will be randomised by the local clinician, in a 1:1 ratio via a remote web based randomisation system, which ensures the allocation sequence is concealed. The randomisation sequence is based on computer generated, random permuted blocks of sizes 2 and 4 and will be blocked by research site. Following completion of randomisation patients will be given a patient card detailing their treatment allocation, which they are asked to carry at all times during the first 6 weeks and to present it to medical staff should they be admitted to hospital during this time on the study.

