### Blinding

Blinding of participants and practitioners is not possible due to the study design. Group allocation will however be concealed to both parties prior to randomisation. Both primary and secondary outcomes are based on self-report questionnaires therefore there will be no investigator bias introduced at assessment stage. Analysis at the primary end point will be conducted blind to group allocation.

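### Permuted blocks of 2 and 4 within each site make allocation partly predictable in this open-label trial and weaken the concealment that the article states

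*Protocol article*

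**What the plan says.** All references are to the protocol article.

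- **Randomisation**, on who allocates and how: "Participants will be randomised by the local clinician, in a 1:1 ratio via a remote web based randomisation system". The sequence uses "random permuted blocks of sizes 2 and 4 and will be blocked by research site". Of the web system the section says: "which ensures the allocation sequence is concealed". The baseline questionnaire is completed before randomisation.
- **Design**: "The trial is a randomised, multicentre, open label, parallel group, pragmatic clinical trial".
- **Blinding**: "Blinding of participants and practitioners is not possible due to the study design". It then adds: "Group allocation will however be concealed to both parties prior to randomisation".
- **General practice recruitment**: at the second appointment, which is set for randomisation and treatment and falls between 24 h and 4 weeks later, the patient's GP "will check for continued eligibility for inclusion and gain written informed consent to study participation".
- **Primary/Secondary care musculoskeletal interface clinics recruitment**: a study clinician informs the patient after the assessment and a study clinician explains the trial. The text does not say that one person takes every step or randomises.
- **Recruitment, screening process and enrolment**: up to 50 sites for 240 participants.
- **Primary analysis at 6 weeks**: the model adjusts for age, sex, symptom duration and baseline score. No site term is listed.

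The Background says that the trial is under way, so the article publishes the block sizes during recruitment or follow-up. The article does not discuss prediction from earlier open allocations.

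**The concern.** Concealment has two parts: nobody can read the list, and nobody can infer the next entry. A remote web system secures the first. The second depends on the sequence. With short blocks inside each site, the running count at that site keeps returning to balance. A clinician who remembers that the last patient had a splint has good reason to expect an injection next.

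This matters at entry, before any outcome is measured. Some eligibility criteria in Table 1 need judgement: symptom severity that calls for a surgical opinion, inability to tolerate the interventions, and illness that in the investigator's opinion precludes participation. A clinician who anticipates the arm can apply these differently, or encourage one patient more than another. The Blinding section's argument that self-report removes investigator bias concerns outcome assessment only and does not reach selection. The primary outcome is self-reported by unblinded participants, and regression adjustment removes only the part of any selection that the covariates capture.

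**Working it through.** The article gives no figure for predictability, so there is none to reproduce. The sample-size calculation is not affected by this point.

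**Inputs.** From the article: 1:1 ratio, blocks of 2 and 4, blocking by site, open label, up to 50 sites, 240 participants. The mean is 240/50 = 4.8 per site if all 50 sites recruit equally. Assumed: each new block has size 2 with probability w = 1/2 (range 1/3 to 2/3), and the observer knows the block sizes and every earlier allocation at the site.

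**Rule.** The best guess is the arm with fewer allocations so far, and a coin toss when the site is balanced.

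**By position at one site, w = 1/2.**

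| Patient | Probability that the best guess is right | Probability that allocation is certain |
|---|---|---|
| 1 | 1/2 = 0.500 | 0 |
| 2 | 1/2 × 1 + 1/2 × 2/3 = 5/6 = 0.833 | 0 |
| 3 | 1/6 × 1 + 5/6 × 1/2 = 7/12 = 0.583 | 1/6 |
| 4 | 1/6 × 1 + 1/2 × 5/6 + 1/3 × 1 = 11/12 = 0.917 | 1/6 |
| 5 | 1/12 × 1 + 11/12 × 1/2 = 13/24 = 0.542 | 1/12 |

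For patient 4 the three terms are: the first two patients had the same arm, so the block has size 4 and its last place is known (1/6); the first block had size 2, so patient 4 is second in a new block (1/2); and a block of 4 was balanced half-way, so its last place is opposite to its third (1/3).

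**Five-patient site.**
- Correct guesses: (0.500 + 0.833 + 0.583 + 0.917 + 0.542)/5 = 3.375/5 = 67.5%.
- Certain allocations: (1/6 + 1/6 + 1/12)/5 = 8.3%.
- Share made when the site is balanced, and so coin tosses: (1 + 0 + 5/6 + 0 + 11/12)/5 = 55%.
- Accuracy when the site is unbalanced: (0.675 − 0.55 × 0.5)/0.45 = 89%.

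**Larger sites.** Exact enumeration gives 71.5% correct and 9.6% certain at 10 patients, and 71.7% and 10.0% at 14. About 45% of allocations are then coin tosses. In the long run a block of 2 yields 0.5 + 1 = 1.5 correct guesses and a block of 4 yields 0.5 + 2/3 + 2/3 + 1 = 2.833, so the rate is (1.5 + 2.833)/(2 + 4) = 72.2%.

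**Sensitivity to w (1/3 to 2/3).** The second patient gets the opposite arm with probability w + (1 − w) × 2/3, which runs from 0.78 to 0.89. Correct guesses run from 67% to 73% and certain allocations from 6% to 12%.

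**What mixing the sizes achieves.** Over complete blocks, certain allocations would be 50% with fixed blocks of 2 and (1/3 + 1)/4 = 33% with fixed blocks of 4, against about 8–10% with the mix. The overall guess rate changes little: 75.0% and 70.8% for the fixed sizes, against 72.2%.

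**Larger blocks kept within site, at 14 patients.** Sizes 4 and 6 give 68% correct and 6% certain. Sizes 4, 6 and 8 give 67% and 2%. The current design gives 72% and 10%.

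**The case against.** The strongest reply is that the article's claim about the web system is literally true, because the list is hidden. Around half of allocations cannot be guessed better than by a coin toss, and first and third patients stand at 50% and 58%. At 4.8 participants per site on average, many sites would sit at the low end of the range. The rates also assume one observer who knows the block sizes and recalls every allocation, and the article does not say whether sites were told the sizes. All of this stands, and it is why the rates are upper bounds.

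The opportunity to steer is also limited. Diagnosis follows a standardised tool, and in the GP pathway eligibility is screened before the second appointment. The 4-week window allows reordering only when two patients are pending at one site. Severity is measured before randomisation and baseline score is in the model. Preference and expectations are collected at baseline. This stands too, but preference and expectations are not in the list of adjustment covariates, and selection on anything unrecorded would remain.

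The average rate also understates the practical issue. A clinician knows when the site is unbalanced, and on those occasions the guess is right about 89% of the time.

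A reader might infer that one clinician confirms eligibility, takes consent and randomises at every site. The GP pathway text supports this. For interface clinics, probably the larger sites, it is inference only.

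**Conclusion.** The point holds as a partial weakness. Site-level blocks of 2 and 4 in an open-label trial let an attentive clinician anticipate allocation better than chance: up to 67.5% correct at a 5-patient site and about 72% at larger sites (67–73% over the assumed block weights), with 83% and 92% for second and fourth patients. The statement that the system ensures concealment is therefore stronger than the design supports.

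A reader might go further and conclude that allocations are largely guessable, that concealment is absent, or that mixing the two sizes does nothing. The figures do not support this. About half of allocations are coin tosses, only about 8–10% are certain (6–12% over the weights), mixing cuts certainty well below that of either fixed size, and the list itself is hidden. Nor do the documents show that any selection took place. They give no basis for turning these rates into a bias in BCTQ points.

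The conclusion rests on the assumed block weights and on the fully informed observer. It supports a cheap improvement to the remaining randomisation and does not invalidate the trial.

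**What to change.** 1. For participants not yet randomised, run the blocks centrally within recruitment pathway (GP practice or interface clinic) instead of within site, with larger mixed sizes that are not disclosed to sites. Site staff would then see only part of the running sequence. Enlarging the blocks but keeping them within site would help only modestly (about 67–68% against 72%).
2. Reword the Randomisation section to say that the web system conceals the list, without claiming that it ensures concealment of each upcoming allocation.
3. Add site to the primary model, for example as a random effect given about 5 participants per site. The listed covariates contain no site term, so this is a change to the model and belongs in the same amendment.
4. For participants already randomised, compare baseline BCTQ and treatment preference or expectations by arm. Balance would be reassuring but could not exclude selection on unrecorded factors.

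The cost is a reconfiguration of the web system, an amendment covering allocation and model, and some within-site imbalance. As a guide to that imbalance, under simple randomisation 2 × 0.5^5 = 6% of 5-patient sites would have a single arm.

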### Blinding

Blinding of participants and practitioners is not possible due to the study design. Group allocation will however be concealed to both parties prior to randomisation. Both primary and secondary outcomes are based on self-report questionnaires therefore there will be no investigator bias introduced at assessment stage. Analysis at the primary end point will be conducted blind to group allocation.

